**Run;**

Where treatment is the treatment group, chg is the change from baseline value of the analysis indicator, and base is the corresponding baseline value.

Lipid panel results were tabulated. Blood pressure test results will be presented in the listing of vital sign test results. Listings of HOMA- $\beta$  and HOMA-IR results were presented in the listing of pharmacodynamic test results.

### **6.5.3 7-point self-measured glucose analysis**

The blood glucose results at each test point of 7-point fingertip glucose at baseline and D85 visit will be summarized by treatment group, and the change curve of 7-point fingertip glucose over the measurement time point will be plotted.

The 7-point fingerstick glucose test results were tabulated.

### **6.5.4 MTT Standard Meal Parameter Analysis**

The parameters for each test point of the MTT standardized meal test were summarized descriptively by treatment group at baseline and D80 visit: insulin, C-peptide, plasma glucose, endogenous OXM, and endogenous GLP-1. MTT standard meal baseline and D80 visit were plotted over time for each parameter. If necessary, calculate the area under the curve (AUC0-4h) between two visits for each parameter and calculate the difference, providing the confidence interval.

MTT standard meal test results were tabulated.

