**Fig. S5: Excursion of glucose, insulin, C peptide, GLP-1 and OXM during MTT at baseline and at week 12.**

**a.** Plasma glucose concentrations excursion during MTT at baseline and at week 12. **b.** Percent change from baseline to week 12 in post-MTT glucose AUC0-4h. **c-d.** Excursion of insulin (c) and C peptide (d) during MTT at baseline and at week 12. **e-f.** Excursion of GLP-1 (e) and OXM (f) during MTT at baseline and at week 12. Data in **a, c, d, e, f** are plotted as means  $\pm$  SEM. Baseline: IBI362 3.0 mg  $n = 8$ ; IBI362 4.5 mg  $n = 8$ ; IBI362 6.0 mg  $n = 8$ ; Pooled placebo  $n = 12$ ; Dulaglutide  $n = 6$ . Week 12: IBI362 3.0 mg  $n = 7$ ; IBI362 4.5 mg  $n = 5$ ; IBI362 6.0 mg  $n = 8$ ; Pooled placebo  $n = 11$ ; Dulaglutide  $n = 6$ . Data in **b** are plotted as LS means  $\pm$  SEM from an MMRM model, with LS means at week 12 shown alongside. IBI362 3.0 mg  $n = 8$ ; IBI362 4.5 mg  $n = 8$ ; IBI362 6.0 mg  $n = 8$ ; Pooled placebo  $n = 12$ ; Dulaglutide  $n = 6$ . CFB = change from baseline; GLP-1 = glucagon like peptide-1; MMRM = mixed-effect model for repeated measures; MTT = mixed meal test; OGIS = oral glucose insulin sensitivity; OXM = oxyntomodulin; SE = standard error of the mean. Source data are provided as a Source Data file.

[figure not shown]

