| 
All efficacy analyses were performed on the efficacy analysis set. Efficacy endpoints will be analyzed only descriptively. For continuous efficacy endpoint indicators, the corresponding means and 95% confidence intervals will be calculated for IBI362 subjects in each dose group, all placebo subjects and all active control subjects, respectively. A two-sample t-test will be used to calculate the p-value of IBI362 versus placebo for each dose group and provide the corresponding point estimate and 95% confidence interval of the difference. LOCF missing values will be used for imputation. For the categorical efficacy endpoints, the ratio within each dose group will be calculated and the 95% confidence interval within the group will be calculated using Clopper-Pearson; the difference between IBI362 placebo groups will be compared using the chi-square test and the corresponding 95% confidence interval will be calculated. Missing values for grouped endpoints will be imputed using the default non-response method.
 | 
Analysis of HbA1c was performed in the efficacy analysis set, analysis of pharmacodynamic parameters was performed in the PD analysis set, and other efficacy endpoint indicators were performed in the safety analysis set unless otherwise specified. For continuous efficacy endpoint indicators, mixed model repeated measures (MMRM)/ANCOVA model was used to estimate the point estimate and 90% confidence interval of each treatment group, and the point estimate and 90% confidence interval of the difference between each IBI362 treatment group/dulaglutide group and placebo. LOCF missing values will be used for imputation. Nominal p-values are provided for comparisons. No multiplicity adjustment will be made in this trial.
 | 
The primary endpoints of this trial are safety and tolerability. The number of subjects in each treatment group is small. 90% confidence interval will be provided. No multiplicity adjustment will be made. Only nominal p value will be provided.
 |

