#### **3.4 PHARMACODYNAMIC PARAMETERS**

- To assess the pharmacodynamic parameters of IBI362 after multiple doses: changes in fasting blood glucose, insulin, fasting C-peptide, HbA1c, endogenous OXM and GLP-1 before and after administration;
- Changes in fasting blood glucose and insulin at steady state in each dose phase during dose escalation;
- The change of each parameter of MTT test from baseline after multiple dose administration;

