### **Run;**

Where treatment is the treatment group, time is each visit, chg is the change from baseline of analysis indicators, and base is the corresponding baseline value. The unstructured correlation was used to estimate the correlation coefficient matrix of change from baseline at each visit for each subject in the MMRM model. The likelihood of the model was constructed using the REML method (SAS proc mixed default likelihood method).

If necessary, MMRM model will be used to estimate the point estimate and 90% confidence interval of each treatment group, and the point estimate and 90% confidence interval of the difference between each IBI362 treatment group/polaglutide group and placebo for other repeated measures efficacy endpoints. Nominal p-values are provided for comparisons.

Results were tabulated.

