### **6.5.2 Analysis of fasting insulin/fasting c-peptide/lipid profile/blood pressure/HOMA-β/HOMA-IR/fasting endogenous OXM/fasting endogenous GLP-1**

The following efficacy indicators after baseline and at D85 visit were descriptively analyzed by treatment group: fasting insulin, fasting c-peptide, blood lipids (triglycerides, total cholesterol, low-density cholesterol and high-density cholesterol), blood pressure (systolic blood pressure, diastolic blood pressure), HOMA-β, HOMA-IR, fasting endogenous OXM and fasting endogenous GLP-1 and their changes from baseline.

If necessary, ANCOVA model will be used to calculate the point estimate and 90% confidence interval of each treatment group and the point estimate and 90% confidence interval of the difference between each IBI362 treatment group/dulaglutide group and placebo. Missing values will be imputed using LOCF in the ANCOVA model and the nominal p-values for the comparisons were provided.

The SAS program for the ANCOVA model can be found at:

```
Proc mixed data = indata method = type3;
```

```
Class treatment (ref ="placebo");
```

Model chg = base treatment;

Lsmeans treatment/diff = control ("placebo") alpha = 0.1;

Ods output lsmeans = datmean diffs = datdiff;

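### SAP 6.5.4 gives the meal-test AUC interval as a difference between visits, with no placebo contrast, so it does not isolate the drug effect

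*Combined protocol and SAP*

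**What the plan says.** SAP 6.5.4 lists five MTT parameters (insulin, C-peptide, plasma glucose, endogenous OXM and endogenous GLP-1), to be "summarized descriptively by treatment group at baseline and D80 visit" and plotted. It then adds a conditional step: if needed, AUC0-4h is calculated "between two visits for each parameter and calculate the difference, providing the confidence interval". The section names no comparator, model, covariate or confidence level.

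Other parts of the SAP do name them:

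- The table of changes in SAP 2.5.2 sets the rule for continuous efficacy endpoints: MMRM or ANCOVA, giving "the point estimate and 90% confidence interval of the difference between each IBI362 treatment group/dulaglutide group and placebo".
- SAP 6.5.1 (HbA1c, fasting glucose) fits an MMRM with the baseline value as covariate and contrasts each IBI362 cohort with placebo at 90% confidence. It allows the same approach, where needed, "for other repeated measures efficacy endpoints". The MTT is not named.
- SAP 6.5.2 codes an ANCOVA with baseline and treatment, placebo as control and alpha 0.1. The MTT is not in its heading or its list of variables.
- SAP 6.9 sends the pharmacodynamic analyses to 6.5.1 and 6.5.2 and does not mention the MTT.

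The MTT is a secondary endpoint in protocol 2.2.2. SAP 3.4 defines it as: "The change of each parameter of MTT test from baseline after multiple dose administration".

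**The concern.** A difference between two visits answers whether patients changed after entering the study. It does not answer whether IBI362 changed them. Patients enter with HbA1c of at least 7.5%, are asked to keep a stable diet and regular exercise, and may take metformin. Regression to the mean and trial participation can therefore move every arm. A randomised placebo group takes the same meal test on the same days, so the comparison that removes the shared change is available without new data.

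What is at stake is interpretation. An AUC interval that excludes zero in an IBI362 arm could be read as a drug effect when part or all of the change is shared with placebo. The MTT is the only standardised meal challenge in the trial, and 6.5.4 is the only section that says how to analyse it. Neighbouring endpoints in the same report carry placebo contrasts, so a reader could easily assume that this interval is one too.

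**Working it through.** **Inputs.** LS mean changes at week 12 with SEs, from Supplementary Table S2 (main efficacy endpoints):

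| | Placebo (n = 12) | IBI362 3.0 mg (n = 8) | Stated difference (90% CI), p |
|---|---|---|---|
| Fasting glucose, mmol/L | -2.52 (0.40) | -3.38 (0.49) | -0.85 (-1.92, 0.21), 0.185 |
| HbA1c, % | -0.87 (0.34) | -1.46 (0.43) | -0.59 (-1.52, 0.35), 0.2941 |

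**Step 1: reproduce the printed contrasts.** Difference = m1 - m0, SE = sqrt(SE1² + SE0²), and t(0.95) = 1.688 with an assumed 36 df (42 patients less 5 groups less 1 covariate).

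- Fasting glucose: -3.38 + 2.52 = -0.86; SE = sqrt(0.49² + 0.40²) = 0.633; 90% CI -1.93 to 0.21; p = 0.182.
- HbA1c: -1.46 + 0.87 = -0.59; SE = sqrt(0.43² + 0.34²) = 0.548; 90% CI -1.52 to 0.34; p = 0.289.

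Both agree with the printed figures apart from rounding and the assumed df, so the group LS means and SEs can be used to compare the two kinds of interval.

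**Step 2: within-group 90% intervals from the same figures** (m ± 1.688 × SE).

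- Placebo fasting glucose: -3.20 to -1.84. Placebo HbA1c: -1.44 to -0.30.
- IBI362 3.0 mg fasting glucose: -4.21 to -2.55. IBI362 3.0 mg HbA1c: -2.19 to -0.73.

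All four exclude zero, including both placebo intervals. Both 3.0 mg contrasts with placebo include zero. The choice of interval therefore changes the reading for this dose. It does not do so everywhere: 4.5 mg on HbA1c (p = 0.0209) and 6.0 mg on fasting glucose (p = 0.0185) have 90% intervals against placebo that exclude zero.

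**Step 3: how often a within-group interval excludes zero when the drug does nothing.** The documents give no placebo change or SD for MTT AUC, so the shared shift is an assumption, expressed in SDs of change (r). For n patients, P = P(|T| > t(0.95, n-1)), where T is noncentral t with n-1 df and noncentrality r × sqrt(n).

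| Shared shift r | n = 8 | n = 7 | n = 5 |
|---|---|---|---|
| 0 | 10% | 10% | 10% |
| 0.25 | 17% | 16% | 14% |
| 0.5 | 36% | 32% | 24% |
| 0.75 | 61% | 55% | 40% |
| 1.0 | 82% | 75% | 58% |

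The columns n = 7, 5 and 8 are the week-12 MTT numbers in the Fig. S5 caption for 3.0, 4.5 and 6.0 mg. A simulated two-sample 90% interval (8 against 12, the same shift in both arms) excludes zero in 10% of trials.

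For scale, taking SD as SE × sqrt(12), placebo HbA1c moved 0.87 / 1.18 = 0.74 SD and placebo fasting glucose 2.52 / 1.39 = 1.8 SD. Placebo body weight moved little: -1.1% (SE 1.0), 90% CI -2.8 to 0.6.

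**The case against.** The strongest defence has four parts.

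**The interval matches the endpoint.** SAP 3.4 defines the MTT endpoint as change from baseline, and an interval for that change has correct coverage. Protocol 9.1 plans no formal testing and the p-values are nominal. This stands. The percentages in Step 3 are not type I error rates of a test in the plan. They show how often the interval would exclude zero for a reason other than the drug.

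**The section does not use the term within-group, and the step is conditional.** This also stands. The reading is inferred from the fact that visits are the only things differenced and no comparator is named.

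**A placebo contrast is available elsewhere.** The rule in 2.5.2 can be read to cover the MTT, and 6.5.1 permits an MMRM for other repeated measures. The caption of Fig. S5b reports percent change in glucose AUC0-4h "from an MMRM model, with LS means at week 12 shown alongside" for all five groups. A reader might therefore go too far in inferring that the MTT cannot show a drug effect under this plan; the documents leave room for the contrast. But the 6.5.1 option does not name the MTT, the Fig. S5b caption mentions no placebo difference, and 6.5.4 specifies neither percent change nor a model. The mismatch remains.

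**The size is borrowed.** Fasting glucose and HbA1c stand in for meal-test AUC, and nothing printed shows a placebo shift in insulin, C-peptide, OXM or GLP-1. That is why Step 3 is given as a range that starts at no shift.

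Two further inferences are tempting and fail. The MTT is not the only postprandial measure, because the 7-point profile includes values 2 hours after each meal. Nor does 6.5.3 share the defect. It states: "The blood glucose results at each test point of 7-point fingertip glucose at baseline and D85 visit will be summarized by treatment group". That is a descriptive summary with a plot, and it offers no interval to misread.

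**Conclusion.** The point holds as a mismatch within the SAP that affects interpretation. On its plain reading, 6.5.4 offers an interval for change between visits, while 2.5.2, 6.5.1 and 6.5.2 use a contrast with placebo. The interval is valid for what it estimates, but it does not separate drug effect from shared change, and the trial's own fasting glucose and HbA1c results show that shared change was real.

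With an assumed shared shift of 0.5 to 1.0 SD, a within-group 90% interval excludes zero in about 36% to 82% of no-effect trials at n = 8, and in 24% to 58% at n = 5, against 10% for a placebo contrast. These figures rest on normally distributed changes and on a placebo MTT shift that the documents do not report. With no shared shift there is no excess.

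The analysis is conditional, nominal and secondary, so the consequence is a possible misreading of the postprandial results. It does not affect the primary safety conclusions. The change is still worth making, because the better method is already written in the SAP.

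**What to change.** In SAP 6.5.4, replace the sentence on AUC0-4h with text that:

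- analyses the change in AUC0-4h at D80 with the ANCOVA of 6.5.2, with baseline AUC0-4h and treatment as terms;
- reports the adjusted difference of each IBI362 group and of dulaglutide versus pooled placebo, with a 90% confidence interval, in line with 2.5.2;
- labels within-group changes as descriptive;
- states how a missing D80 test is handled. The ANCOVA in 6.5.2 uses LOCF, but the schedule has only one planned post-baseline MTT, and the Fig. S5 caption shows 5 of 8 patients with a week-12 test at 4.5 mg.

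No change to 6.5.3 is needed. The cost is SAP wording and a few lines of code on data already collected. The placebo-contrast interval may be wider than the visit-difference interval, and the result less favourable. Since results are already printed, an analysis added now should be labelled as specified after the data were seen.

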## **6.6 SAFETY ANALYSIS**

Safety analysis will be performed in the safety analysis set and grouped by actual treatment received.

### **6.6.1 Adverse events**

Classified by date of event:

- Pre-treatment Adverse Events: Adverse events that occurred from signing of informed consent until the first dose of study treatment.
- Treatment-emergent adverse events (TEAEs): Adverse events that occurred or became serious during the first dose of study treatment through 56 days after last dose.
- Post-treatment adverse events: Adverse events that occurred or became serious after 56 days following the last dose until the end of the trial.

If the AE start date is completely/partially missing, impute the date according to Section 5.3 before assigning pre-treatment/on-treatment/post-treatment adverse events.

The incidence (frequency) of all AEs, TEAEs, severe TEAEs, TEAEs leading to permanent treatment discontinuation, drug-related TEAEs (TRAEs), severe TRAEs, TRAEs leading to permanent treatment discontinuation, AESIs, severe AESIs, AESIs leading to permanent treatment discontinuation, SAEs, SAEs related to study drug, and SAEs leading to permanent treatment discontinuation will be summarized by treatment group.

The following categories of adverse events will be summarized by SOC, PT, and SOC, PT, and severity from MedDRA coding:

- TEAEs
- TEAE leading to permanent discontinuation
- TRAE
- TRAEs leading to permanent discontinuation
- AESI
- AESIs leading to permanent discontinuation
- For gastrointestinal reactions, the number of events with gastrointestinal reactions was also provided. Gastrointestinal reactions including adverse reactions with preferred terms of nausea, vomiting, diarrhea, dyspepsia, abdominal distension, abdominal discomfort, and gastroesophageal distress

TEAEs will also be summarized by PT in MedDRA and the number of events of TEAEs will be calculated.

Treatment-emergent SAEs, treatment-emergent SAEs related to study drug, and treatment-emergent SAEs leading to permanent discontinuation will be summarized by SOC and PT.

Hypoglycemic events will be summarized by treatment group.

The above summary tables are sorted according to the incidence of AEs in all subjects who received IBI362.

Subjects who discontinued treatment due to AEs, subjects who experienced SAEs, and subjects who died will be listed (at least include AE start date, end date, severity, relationship with drug, action taken, and outcome). All AEs will be listed.

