## 3.2 Phase 1b/2 Study Design

### 3.2.1 Overall Study Design

The study will be planned to include 42 patients with type 2 diabetes who failed to control HbA1c after at least 2 months of lifestyle intervention or stable dose of metformin ( $\geq 1000$  mg/day or maximum tolerated dose). The study will be divided into three cohorts, which will be Cohort 1 (n = 14), Cohort 2 (n = 14) and Cohort 3 (n = 14). Patients in each cohort will be randomized 8:4:2 to IBI362 group (n = 8), placebo group (n = 4), or dulaglutide 1.5 mg group (n = 2). The active control, dulaglutide, will be administered as 1.5 mg once-weekly for 12 weeks in Cohorts 1, 2 and 3, and the dosing schedules for IBI362 and placebo are described below:

**Cohort 1:** Patients randomized to IBI362 or placebo initiate treatment with 1.0 mg once-weekly with dose escalations every 4 weeks by 1 mg until the maintenance dose (3.0 mg) will be achieved.

**Cohort 2:** Patients randomized to IBI362 or placebo initiate treatment with 1.5 mg once-weekly with dose escalations every 4 weeks by 1.5 mg until the maintenance dose (4.5 mg) will be achieved.

If the patient failed tolerate 3.0 mg or 4.5 mg with the met discontinuation criteria, the patient needs to explore the next dose according to Cohort 2 (backup 1) or Cohort 2 (backup 2).

**Cohort 2 (backup 1):** With the tolerated dose of 3.0 mg, the dose should be reduced to 2.25 mg after 1-week break and treat with it for 2 weeks. After that, if it is well-tolerated, the dose will be increased to 3.0 mg and treat for 4 weeks.

**Cohort 2 (backup 2):** If the dose of 4.5 mg is intolerable to the patient, the dose should be reduced to 3.75 mg after 1-week break and administered continuously for 2 weeks till the end of the trial.

**Cohort 3:** Dosing should not be started until the patients in Cohort 2 complete the 4-week tolerability evaluation of 1.5 mg. If 1.5 mg is not well-tolerated, 2.0 mg and higher doses in Cohort 3 will not be explored. Patients randomized to IBI362 or placebo initiate treatment with 2.0 mg once-weekly with dose escalations every 4 weeks by 2.0 mg until the maintenance dose (6.0 mg) will be achieved.

The study will consist of a 3-week screening period, a 12-week double-blind treatment period, and an 8-week follow-up period.

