## 8. safety reporting and adverse event management

### 8.1 Definition of Adverse Events

An adverse event (AE) is defined as any untoward medical occurrence, whether or not there is a causal relationship with the study drug, in a clinical study subject from the time informed consent form is signed through 90 days after the last dose of study drug, and includes, but is not limited to, the following:

- Exacerbation of pre-existing (prior to clinical study) medical conditions/diseases (including worsening of symptoms, signs, laboratory abnormalities);

- Any newly developed adverse medical conditions (including symptoms, signs and newly diagnosed diseases);
- Clinically significant abnormal laboratory values or results.

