### **8.6.1 Timely collection of adverse events**

The investigator learns of an adverse event by asking the patient a non-inductive question.

All AEs, including SAEs, whether observed by the investigator or spontaneously reported by the patient, will be collected from the signing of the ICF through the end of the study. After the end of the study, if the investigator learns of a patient's serious adverse event related to the study drug or procedure, it should also be reported to the sponsor.

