#### 8.6.3 Contents of adverse event records

The investigator should completely record any AE, including diagnosis (if no diagnosis, record the symptoms and signs including laboratory abnormalities), start and stop time (if applicable), severity and changes, whether it is an SAE, actions taken for the study drug, treatment given due to AE and the outcome of the event, and the relationship between the AE and the study drug.

For serious adverse events, the investigator provided the date on which the AE met the criteria for an SAE, the date that the investigator became aware of the SAE, the rationale for determining the AE as an SAE, the date of hospitalization, the date of discharge, the possible cause of death, the date of death, whether an autopsy will be performed, the assessment of causality with the study procedures, the assessment of causality with other drugs, and other possible causes of the SAE. The investigator should provide the basis for judging the correlation and the description of SAE. The description of an SAE should also include the patient's number, age, gender, height and weight; the patient's indications for the investigational drug treatment, disease stage and relevant general conditions; the clinical course of the SAE including its occurrence, development, outcome and results; laboratory test results related to the SAE (the test time, unit and normal range must be provided); past history related to the SAE, concomitant diseases and their occurrence and duration; medication history related to the SAE, concomitant drugs and their start, duration, dosage and administration; and details about the start, duration, dosage and administration of the investigational drug treatment.

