### **Pre-existing medical conditions**

The preexisting symptoms/signs a patient has already presented during the screening period of the trial should be recorded and reported as AEs only when there is worsening in severity, frequency or nature (except for worsening of the medical condition under study) after entry into the trial. Changes from the previous state will be reflected in the record, such as "increased frequency of headache".

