| ICF          | Informed consent form                           |
| ICH          | International Conference on Harmonisation       |
| IDF          | International Diabetes Federation               |
| INR          | International normalized ratio                  |
| LDH          | Lactate dehydrogenase                           |
| LDL-C        | Low density liprotein cholesterol               |
| MedDRA       | Medical Dictionary for Regulatory Activities    |
| MTD          | Maximum tolerated dose                          |
| Nab          | Neutralizing Antibody                           |
| NIA          | National Institute on Aging                     |
| OXM          | Oxyntomodulin                                   |
| PLT          | Platelet                                        |
| PT           | Prothrombin time                                |
| RBC          | Red Blood Cell                                  |
| SAE          | Severe Adverse Event                            |

|              |                                       |
|--------------|---------------------------------------|
| SOPs         | Standard Operation Procedure          |
| T2DM         | Type 2 diabetes mellitus              |
| TBIL         | Total bilirubin                       |
| TC           | Total cholesterol                     |
| TEAEs        | Treatment Emergent Adverse Event      |
| TG           | Triglyceride                          |
| TIA          | Transient ischemic attack             |
| TSH          | Thyroid Stimulating Hormone           |
| UA           | Uric Acid                             |
| Vd           | Volume of distribution                |
| WBC          | White blood cell                      |
| WT           | Wild type                             |
| Abbreviation | English full name                     |
| ADA          | Anti-drug antibody                    |
| AE           | Adverse Event                         |
| AESI         | Adverse Event of Special Interest     |
| ALB          | Albumin                               |
| ALP          | Alkaline phosphatase                  |
| ALT          | Alanine transaminase                  |
| APTT         | Activated partial thromboplastin time |
| AR           | Accumulation Ratio                    |
| AST          | Aspartate amino transferase           |
| AUC          | Area Under Curve                      |
| CK           | Creatine Kinase                       |

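### The SAP's treatment-emergent rule has no route for a pre-dose adverse event that worsens on treatment without becoming serious

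*Combined protocol and SAP*

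**What the plan says.** SAP 6.6.1 sorts adverse events by date into three classes. Pre-treatment events are "Adverse events that occurred from signing of informed consent until the first dose of study treatment". Treatment-emergent events are "Adverse events that occurred or became serious during the first dose of study treatment through 56 days after last dose". Post-treatment events use the same two limbs, onset or becoming serious, for the time after those 56 days. Nothing else in the SAP adds worsening as a route into the TEAE set; section 5.3 deals only with missing dates, causality and severity. The protocol uses the term TEAE without defining it.

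Events can begin before dosing and be on file. Under protocol 8.6.1 all adverse events "will be collected from the signing of the ICF through the end of the study", and protocol 3.2.1 states: "The study will consist of a 3-week screening period, a 12-week double-blind treatment period, and an 8-week follow-up period".

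Three recording rules matter:

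- Protocol 8.6.3 asks that each record give, among other items, "start and stop time (if applicable), severity and changes, whether it is an SAE".
- The note on ongoing or recurrent events asks for separate entries when an event resolves and comes back. It does not ask for one when a persistent event gets worse.
- The note on pre-existing conditions says that symptoms already present in screening "should be recorded and reported as AEs only when there is worsening in severity, frequency or nature".

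The SAP abbreviation list expands SAE as "Severe Adverse Event". The protocol's own list has it as serious.

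**The concern.** Seriousness and severity are separate scales in this protocol. Section 8.2 defines seriousness by outcome (death, hospitalisation and the like); section 8.4 grades severity as mild, moderate or severe. Sections 3.2.3 and 8.3 both single out events that are severe, drug-related and not serious. The TEAE rule refers only to the first scale.

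The primary endpoint in protocol 2.2.1 is the incidence and severity of adverse events at each dose level, and drug-induced aggravation of an existing complaint is part of that. Where the rule misses such an event, it can only lower the TEAE count. This also runs against the SAP's cautious handling elsewhere: section 5.3 treats an event with unclear onset as treatment-emergent, missing causality as related and missing severity as severe. The supplement's full adverse event table, Table S3, is a TEAE table, so this definition governs the main display.

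**Working it through.** The plan gives no figure for this point, so the check is to apply the written rules to each possible case.

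1. **Onset on or after first dose, within the window.** TEAE by the onset limb.
2. **Onset before first dose, becomes serious in the window.** TEAE by the second limb.
3. **Symptom present in screening, worsening entered as an adverse event with an on-treatment start date.** This follows the note on pre-existing conditions. The entry has its onset in the window, so it is a TEAE.
4. **Adverse event opened before first dose, worsens in severity in the window, never serious, kept on one record.** The start date is pre-dose and the serious limb is not met, so it remains a pre-treatment event. It is missing from the TEAE, severe TEAE and drug-related TEAE summaries, including those by system organ class, preferred term and severity, and those for discontinuation.

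Case 4 is permitted by the documents: 8.6.3 keeps severity changes inside the record, and only recurrence calls for a separate one.

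What still captures a case 4 event:

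- SAP 6.6.1 gives an overall incidence of all AEs and lists every AE. The all-AE figure is not broken down by class, term or severity, and it also counts events that were purely pre-dose.
- SAP 6.6.1 tabulates events of special interest by class, term and severity, with no stated restriction to TEAEs. Protocol 8.3 puts nausea, vomiting, decreased appetite, hypoglycemia and other named events in this group, together with any severe, related, non-serious event.
- SAP 6.6.2 cross-tabulates baseline against the worst post-baseline laboratory result.

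What is left is mainly a case 4 event that is not of special interest. An example is back pain that is mild in screening and becomes moderate on treatment: it would appear only in the all-AE count and the listing.

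**Weight of one patient.** Arm sizes follow from the 8:4:2 allocation in three cohorts (protocol 9.2):

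- IBI362, each arm: n = 8, so 1/8 = 12.5 percentage points.
- Pooled placebo: n = 3 × 4 = 12, so 1/12 = 8.3 points.
- Pooled dulaglutide: n = 3 × 2 = 6, so 1/6 = 16.7 points.

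These are maxima for a single table row. A patient already counted in that row changes nothing. For example, Table S3 has 8 of 8 patients with any TEAE in the 4.5 mg arm, so that row cannot rise.

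**The case against.** The strongest reply is that the protocol already handles worsening. The note on pre-existing conditions makes an increase in severity, frequency or nature the reportable event, and it draws no line between a symptom noted in screening and an adverse event recorded there. A site that applies it broadly, with the date of worsening as onset, produces a TEAE under the existing text. This stands in part: the loss is not automatic. But neither document says whether worsening of an already recorded event opens a new record, so the TEAE count would depend on site habit.

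A second reply is that the wording may be a slip. The SAP expands SAE with the word severe, so its second limb may have been meant as becoming severe, or simply worsening. The documents do not settle this. SAP 6.6.1 lists severe TEAEs and SAEs as separate rows, so a programmer would reasonably read the limb as seriousness. If it did mean becoming severe, mild-to-moderate worsening would still be left out.

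Some stronger readings are tempting but unsupported:

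- *That such events vanish from the safety reporting.* They stay in the all-AE count and the listing, and in the special-interest tables where they qualify.
- *That the rule contradicts protocol 8.1.* That section defines an adverse event, not a treatment-emergent one. By treating exacerbation of a prior condition as an adverse event, it helps close the gap.
- *That the maximum tolerated dose is affected.* The criterion in 3.2.3 for severe, related, non-serious events does not depend on TEAE status. The criterion for serious events does use the term, but an event that becomes serious is already covered by the SAP rule.
- *That a bias can be calculated.* Screening allows at most 21 × 42 = 882 patient-days, but that is time, not events. The documents give no rate of pre-dose events that later worsen, so any assumed number of patients per arm would have no basis.

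**Conclusion.** The gap is real but conditional. As written, SAP 6.6.1 leaves an adverse event with pre-dose onset out of the TEAE, severe TEAE and drug-related TEAE tables if it worsens on treatment, does not become serious and stays on its original record. The main exposure is events that are not of special interest, chiefly those going from mild to moderate.

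The number of affected patients is not stated and could be zero, and nothing in the documents shows that Table S3 is in error. Each affected patient would change a row by at most 12.5 points in an IBI362 arm, 8.3 in pooled placebo or 16.7 in dulaglutide. The conclusion assumes that the second limb means seriousness as in protocol 8.2, and that sites did not open a new record when an event worsened. The rule should be corrected because it can give a wrong count for the primary endpoint and the remedy is small.

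**What to change.** In SAP 6.6.1, define a TEAE as an adverse event with onset, or with worsening in severity (or becoming serious) relative to its pre-dose state, from first dose through 56 days after last dose. In the post-treatment definition, replace the becoming-serious limb with matching worsening wording.

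Choose one recording method and state it:

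- keep one record, counted once at its worst on-treatment grade; or
- open a new record at the date of worsening.

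Doing both could count the same event twice. The first option relies on the severity changes that protocol 8.6.3 already asks sites to record. The second needs a line in the eCRF completion guide.

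Correct the SAP's expansion of SAE to serious adverse event. One data query, for events with pre-dose onset and a later rise in severity, would show whether any patient is affected.

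The cost is a short text change and that query. Reported TEAE rates may rise slightly.
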